### Design

This project will be conducted in three phases over 24 months in a sample of older adults from Hong Kong. Phase 1 (Months 1 to 4) – Development of intervention using the HAPA theory and preparation for data collection including participant recruitment and preparation of materials and measures. Recruitment will overlap with Phase 2 until the required sample size has been recruited. Phase 2 (Months 4 to 20) – Implementation of the intervention including baseline measures, intervention administration through telephone, ongoing follow-up outcome (See Fig. 1). Phase 3 (Months 21 to 24) – Evaluation of intervention through: (a) evaluating the immediate impact through effects on outcomes at 6-month post-intervention; (b) evaluating the long-term impact of the intervention through effects on outcomes at 12-month follow up; and (c) assessing the compliance of the participants with the intervention.

**Fig. 1 Fig1:**
[figure not shown]
Study design

### Phase 1: intervention development

The rationale of the intervention development will be in developing increased motivation to adopt influenza preventive behaviors in Hong Kong older adults and assisting them in converting their motives into action and maintaining the behavior [16, 22]. According to the HAPA theory, motivation is a necessary but not sufficient condition for action initiation and persistence; people also need to identify effective plans to enact their intentions or motives. The protocol will therefore include intervention components that promote motivation (action self-efficacy, risk perception, and outcome expectancy) and planning (action and coping planning, maintenance and recovery self-efficacy).

Aims of the first phase are: (i) develop the content of the HAPA-based intervention to promote the influenza prevention behaviors of Hong Kong older adults building on our previous projects on influenza and influenza prevention; (ii) design an intervention training manual so that the intervention can be administered consistently across groups and replicated by others; (iii) develop the intervention delivery protocol consistent with the design of randomized controlled trial; (iv) develop measures of key outcome variables to be used to evaluate the effectiveness of the intervention; and (v) confirm participation of elderly centers (i.e., government-established elderly care facilities) to be involved in the intervention and secure ethical clearance for the study. Prior to the start of the project upon funded, the study protocol has been registered in CCRB Clinical Trials Registry of the Chinese University of Hong Kong, a Partner Registry of a WHO Primary Registry (Ref: CUHK_CCRB00567). Main components and example content of the study protocol are listed below.

#### Behavior initiation

Several motivational strategies of behavior initiation will be included: (a) The information-giving component will include a slide presentation from the facilitator to the group promoting the advantages, and negating the disadvantages, of influenza prevention for health and outlining the risk levels of influenza for older adults (targeting risk perception); a ‘how to’ education unit aimed at providing information about how to conduct influenza prevention behaviors in certain scenario, such as covering both mouth and nose when wearing facemasks instead of solely on month in a crowded place during peak of flu (targeting action self-efficacy); and a brief example of an influenza prevention program and possible outcomes and gains of engaging in regular influenza prevention behaviors (targeting positive outcome expectancy); (b) In the goal-setting exercise, participants will be given guidance on how to set a goal of adopting influenza prevention (targeting action self-efficacy). They will be told that the aim is to develop personal goals for increasing their influenza prevention behaviors, and participants will be encouraged to set goals realistic short- and long-term goals; (c) In the ‘mental simulation’ activity, participants will be asked to visualize the actions they would need to perform to achieve their goals and how they would feel once they had achieved those goals (targeting positive outcome expectancy); and (d) In the implementation intention activity participants will be asked to set specific action plans of when, where, and in which situations they will adopt influenza prevention behaviors and tying it in with everyday occurrences to remind them to implement their plan (targeting planning).

#### Behavior maintenance

Several strategies will be introduced in the maintenance session and be compared with the concepts at the initiation session [22]: (a) maintenance/relapse prevention self-efficacy instead of action self-efficacy, that is, building the confidence in overcoming barriers to continue the influenza prevention behaviors (e.g., avoiding embarrassment of wearing a facemask in a public place); (b) coping planning should be emphasized rather than simply focused on action planning, this is because that the established new behavior patterns might be threatened by previous habits and some specific situations; (c) the feelings of enjoyment/satisfaction in complying to the influenza prevention behaviors will be emphasized rather than the expectations of the benefits of influenza prevention behaviors, this because perceived satisfaction has long been demonstrated as a significant predictor of behavior maintenance; and (d) participants will be encouraged to actively seeking social support from their networks, which will replace the support from the project facilitator when the project is withdrawn.

#### Control group

Participants randomly assigned to the control group will not receive the behavior-change components of the telephone-delivered intervention sessions. Indeed, participants in the control group will receive some general information on influenza prevention in the group-delivered preliminary session. But, the behavior-change aspects of the information-giving component, goal-setting, mental-simulation, and implementation intention components will be absent from the control group as they will not receive the telephone-delivered intervention sessions. The part-time research assistants will be provided with training and a feedback session to ensure consistency in delivering the intervention.

### Phase 2 – implementation of the intervention

#### Sample size

We will assume a small effect size (Cohen’s *d* = .20) for the effect of the intervention in order to calculate a conservative post-intervention sample size sufficient to detect an effect. G*Power analysis using the between-factor (i.e., 3 groups) repeated measures (i.e., 4 phases; baseline, 3-month, 6-month, and 12-month measurements) multivariate analysis of variance (MANOVA) indicates that a sample size of 65 in each group is required at follow-up in order to detect a small effect size (*d* = .20) in the outcome variables with power (beta) set at .90 and significance level (alpha) set at .017 (i.e., .05/3). Based on conservative estimate of 25% attrition rates, we aim to recruit 261 participants at baseline (*n* = 87 participants per group).

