#### Data analysis

Data will be stored in password-protected spreadsheets saved on a computer of a member of the research team. Data will be initially treated for missing values with multiple imputation. The distribution of the data will be examined that the skewed data will be log-transformed and replaced with median (interquartile range). All analyses will be conducted using full intention-to-treat analyses with scores on dependent variables for non-compliers carried over using the last-observation carried forward method. Independent samples t-tests and chi-square analysis will be used to test whether there are significant differences between non-compliers and compliers. We will analyze the effectiveness of the intervention using a series of linear mixed models on each behavioral and psychological outcome variable. In the analyses, four phases will be the within-participants factor and three intervention conditions will be the between-participants factor. Baseline scores for the dependent variables will be included as covariates in the analysis with salient demographic variables: age, gender, marital status, education level, and socioeconomic status. We will use Akaike and Bayesian information criteria to assess whether a compound symmetry covariance structure will provide the best model fit of each outcome variable. The phase (i.e., time of measurement) by intervention condition (i.e., behavior initiation + behavior maintenance; behavior initiation only; and control group) interaction will be the central test. Beyond main effects of the intervention, we will also test whether there are any statistically significant interactions between the intervention condition and the time factor. For all tests, the Cohen’s d effect size will be calculated associated with a 95% confidence interval. Structural equation modelling (SEM) will be used to test the hypothesized theoretical sequence in the HAPA model [25]. In the analyses, the effect of the intervention group conditions will be included using a dummy coded variable along with the demographic and baseline variables. The 95% bias corrected (BC) bootstrapping method (with *n* = 5000 bootstrap resamples) was subsequently employed to test the indirect effects of mediators (e.g., intention, maintenance and recovery self-efficacy, action and coping planning) (25). The CONSORT Extension for Nonpharmacological Treatment Interventions will be followed to report the results.

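### 65 per group does not give 90% power for Cohen's d = .20 at alpha .017 at any plausible correlation among the repeated measurements

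*Protocol article*

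**What the plan says.** The Sample size section assumes a small effect, Cohen's d = .20, and presents the resulting number as conservative. It uses a G*Power calculation for a repeated-measures MANOVA with a between factor of three groups and four occasions (baseline, 3, 6 and 12 months). It concludes that "a sample size of 65 in each group is required at follow-up in order to detect a small effect size", "with power (beta) set at .90 and significance level (alpha) set at .017 (i.e., .05/3"). After 25% attrition, "we aim to recruit 261 participants at baseline", 87 per group. It gives neither the correlation among the four measurements nor the way d was turned into the effect-size index of an F test.

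The Data analysis section plans linear mixed models with the baseline score as covariate. It says that the phase-by-condition "interaction will be the central test". It also commits to reporting Cohen's d with a 95% confidence interval for all tests. Hypotheses (a) and (b) are comparisons between arms, and (b) sets the two active arms against each other.

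**The concern.** Cohen's d is a standardised difference between two means. A between-group d of .20 normally needs several hundred participants per arm, so 65 per arm at a Bonferroni-reduced alpha is surprising even with repeated measures. Power is the only justification offered for the sample size. If the figure is wrong, funders and readers are told that the trial can detect an effect that it will probably miss. This is a stated number and not an omitted detail, so an unseen analysis plan cannot put it right.

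**Working it through.** **Inputs.** From Sample size: d = .20, alpha = .017, power .90 (labelled beta in the text), 3 groups, m = 4 occasions, 65 per group (N = 195), 25% attrition. From Data analysis: baseline covariate, interaction as central test. Assumed: two-sided pairwise tests, and an equal correlation r between all occasions, shown as a range.

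**1. Attrition.** 65/.75 = 86.7, rounded up to 87; 3 × 87 = 261. This reproduces.

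**2. What yields 65.**
- Between-factor test, F(2, N − 3), noncentrality λ = N·m·f²/(1 + (m − 1)r). With f = .20 and r = .3: λ = 195 × 4 × .04/1.9 = 16.42, power 90.4%. With 64 per group power is 89.9%, so 65 is exactly the required integer. But f = .20 means d = 2f = .40 for two groups. For three groups it means .42 (two arms equal, one apart: .20 × 3/√2) or .49 (evenly spaced, extreme arms: .20 × √6).
- Interaction in repeated-measures ANOVA form, F(6, 576), λ = N·m·f²/(1 − r). With f = .10 and r = .64: λ = 7.8/.36 = 21.7, power 90%. Under a sustained effect in both active arms, f = .10 corresponds to d of about .49 (step 5).

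**3. The stated between-factor test with d = .20.** Take f = d/2 = .10. This is generous, because three-group patterns with a largest difference of .20 give f of .082 to .094. Then λ = 7.8/(1 + 3r):

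| r | λ | Power |
|---|---|---|
| 0 | 7.80 | 54% |
| .3 | 4.11 | 26% |
| .5 | 3.12 | 19% |

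Power falls as r rises, so 90% is not reached at any r ≥ 0.

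**4. Pairwise contrasts, 65 against 65, noncentral t, noncentrality d/√(2v/65).** The residual variance v is 1 − r² for one baseline-adjusted follow-up and (1 + 2r)/3 − r² for the baseline-adjusted mean of three.

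| r | v, one visit | Power | v, three-visit mean | Power |
|---|---|---|---|---|
| .3 | .910 | 11% | .443 | 24% |
| .5 | .750 | 14% | .417 | 26% |
| .7 | .510 | 21% | .310 | 36% |
| .8 | .360 | 31% | .227 | 49% |

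Reaching 90% would need r of about .95 (one visit) or .92 (three-visit mean). Unadjusted at one visit (v = 1), power is about 10%, and 90% would take 2(2.387 + 1.282)²/.04, about 673 per arm.

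**5. The interaction.** Suppose d = .20 in both active arms at all three follow-ups. Group deviations are (1/3, 1/3, −2/3) and time deviations (−3/4, 1/4, 1/4, 1/4). Their sums of squares are 2/3 and 3/4, so f² = .04 × (2/3) × (3/4)/12 = .00167 and f = .041. Then λ = 195 × 4 × .00167/(1 − r) = 1.3/(1 − r). Power is 6% (r = .3), 9% (.5), 16% (.7) and 27% (.8). Conversely, f = .10 needs d = .20 × .10/.041, about .49.

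**6. Detectable d at 90% power, 65 per arm, alpha .017 (noncentral t).** About .65 unadjusted at one visit; .56 for one adjusted follow-up and .42 for the adjusted three-visit mean, both at r = .5.

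**The case against.** The best defence is that 65 came from a legitimate run of the software. Converting d = .20 to f = .10 in the usual way and entering it for the interaction, which is the central test, gives 90% power at r of about .64 and more above that. This stands as a possible origin of the number. It does not rescue the sentence, because that f is not produced by a mean difference of .20 between arms, and the section describes a between-factor test. It does mean that a reader who concludes that f was certainly mistaken for d goes further than the document allows. The correlation and conversion are not shown, so the cause cannot be settled.

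The interaction figures also depend on the assumed pattern. If initiation-only stays at .20 while the combined arm has .20 at 3 months and .40 at 6 and 12 months, f² = .005 and λ = 3.9/(1 − r). Power is then about 35% (r = .5), 63% (.7) and 86% (.8). That pattern includes an effect twice the stated one, so it is no support for d = .20.

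Three stronger readings are tempting:
- That the trial has 10% power. This figure belongs to an unadjusted single-visit t-test, which is not the planned analysis.
- That a null result will be taken to exclude a small effect. The document does not say so, and the promised 95% interval for d (half-width about 1.96 × √(2/65) = .34 at one visit, unadjusted) would show readers otherwise.
- That only medium-to-large effects are detectable. The .42 for the adjusted three-visit average lies below that.

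**Conclusion.** The power statement is wrong and should be corrected. For a between-group d of .20 at two-sided alpha .017 with 65 per group, every reading examined falls well short of 90% at plausible correlations. Over r = .3 to .8, the planned kinds of analysis (baseline-adjusted contrasts and the interaction under a sustained effect) give roughly 6% to 49%. The stated between-factor test gives at most 54%, at r = 0. The two routes that do produce 65 correspond to a d of about .40 to .49, at least double the stated effect. These results assume equal correlations across occasions and, for the interaction, the same sustained effect in both active arms. The attrition step and the total of 261 are arithmetically sound.

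**What to change.** Keep 261 enrolled and rewrite the sample-size paragraph:
- State whether the effect size is d or f, which contrast or effect is tested, and the correlation assumed among measurements.
- Replace the d = .20 claim with the d detectable at 90% power for 65 per group at alpha .017: about .42 for the baseline-adjusted average of three follow-ups and .56 for one adjusted follow-up (both at r = .5), and about .65 for one unadjusted visit.
- Remove *small* and *conservative* from the effect-size claim.

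Recomputing N for d = .20 would also be coherent, but it means a much larger trial and is not needed to make the statement true. The cost of the rewording is that the stated detectable effect becomes less favourable.

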#### Recruitment strategy

Given the links the research team has established with the elderly centers (including District Elderly Community Centers, Neighborhood Elderly Centre) in our previous projects, we will make contacts (i.e., phones, emails, and faxes) with center-in-charges and employ their support in championing recruitment to the study. We plan to recruit participants who are registered as members of the elderly centers at the three main territories of Hong Kong (i.e., Hong Kong Island, Kowloon, and New Territories).

#### Preliminary group-based education session

Interested participants will be invited to attend an initial session where they will be screened for eligibility and be provided with full details of the study and an information and consent form pack. Participants will also be invited to participate in a one-off group education session on the general information about types of influenza, peak influenza season, routes of influenza transmission, and influenza preventive behaviors. Participants will then be randomized into one of the three conditions: (a) “behavior initiation” and (b) “behavior initiation + behavior maintenance”, and (c) “control group”. Randomisation will be conducted by a research staff who is blind to the composition of the participants using the online randomisation tool. Participants will be blinded to the intervention allocation, while the part-time research assistants will be blinded to the research purpose.

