## Methods

### Participants

Participants in the current study will comprise Hong Kong Chinese older adults. Participants will be eligible if they are 65 years or over; retired or homemakers; willing to be randomly assigned to experimental or control groups; able to understand the study rationale; a first-language Cantonese-speaker; and, most importantly, non-vaccinated within 1 year and report never or rarely adopting any of the influenza prevention behaviors listed by the research group. Participants who report more frequent preventive behaviors will not be invited to attend the preliminary session. We will also exclude older adults who are dementia as well as who are fragile to move.

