#### Telephone-delivered individual behavior initiation sessions

Participants in (a) “behavior initiation” and (b) “behavior initiation + behavior maintenance” intervention groups will receive telephone-delivered intervention sessions at weekly intervals throughout the course of behavior initiation for 3 months. The purpose of these is to serve to remind participants of their influenza prevention goal and their action plans to implement them, mainly focused on the motivational stage. The intervention sessions will be administered by telephone lasting 10 to 20 min, and will be audio-recorded with the permission from participants for fidelity checks. To the extent that participants will have talked about their appropriate influenza prevention goals in the goal setting, mental simulation, and action planning exercises, step-by-step personal instructions and feelings about pursuing their goal, and when and where they will pursue their goals. Participants in the control group will not receive the telephone-delivered intervention sessions. Part-time research assistants will be recruited to deliver the telephone intervention sessions appropriately 10–15 min. They were be trained by, and receive feedback from, the PI and project coordinator and practice with each other in simulated scenarios.

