#### Telephone-delivered individual behavior maintenance sessions

Following the behavior initiation session, all participants will be asked to report the three influenza prevention behaviors via telephone calls in three randomly-selected days in 9 days, clinical influenza episodes as well as flu-like symptoms in the past 3 months, and then they will again be invited to complete the same set of psychological outcome measures administered at baseline. Thereafter that only participants allocated to the “behavior initiation + behavior maintenance” intervention group will continue to receive telephone-delivered intervention sessions at weekly intervals for 3 months. The sessions will focus on strategies of behavior maintenance at the volitional stage.

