#### Follow-up measures

At the 3-month (i.e., the middle time point of the intervention after the behavior initiation session), 6-month (post-intervention), and 12-month follow-up occasions, participants will receive the same set of psychological outcome measures administered at baseline. They will also be asked to report the three influenza prevention behaviors (i.e., washing hands, avoid touching eyes, nose or mouth, and facemask wearing) as well as whether they get vaccinated via telephone calls in three randomly-selected days in 9 days. Participants’ self-reported clinical influenza episodes as well as flu-like symptoms during the past 3 months will also be collected. Participants will be reminded of their follow-up visit by telephone in advance of their visit. In order to minimize attrition, in particular participants from the control group, a fixed amount of monetary reward will be provided to those who completed all assessments.

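### Participants cannot be blinded to allocation when they know the study design and get weekly coaching calls or none, and blinding assistants to the purpose does not protect self-reported outcomes

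*Protocol article*

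**What the plan says.** The blinding statement is in the section on the preliminary group-based education session: "Participants will be blinded to the intervention allocation, while the part-time research assistants will be blinded to the research purpose". Nothing is said about blinding the assistants to allocation.

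The same section says that people attending the initial session will "be provided with full details of the study and an information and consent form pack". The eligibility criteria under Participants require that they be "willing to be randomly assigned to experimental or control groups".

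Contact after randomisation differs by arm:
- **Control:** "Participants in the control group will not receive the telephone-delivered intervention sessions". The Control group section confirms that these participants get only general information at the group session.
- **Both active arms, first 3 months:** they "will receive telephone-delivered intervention sessions at weekly intervals throughout the course of behavior initiation for 3 months".
- **Initiation + maintenance only, next 3 months:** this "intervention group will continue to receive telephone-delivered intervention sessions at weekly intervals for 3 months".

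The part-time research assistants deliver the telephone sessions. On their preparation: "The part-time research assistants will be provided with training and a feedback session to ensure consistency in delivering the intervention".

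On the outcomes, Follow-up measures says of participants: "They will also be asked to report the three influenza prevention behaviors". Vaccination is asked about in the same telephone calls, made on three random days out of nine. Outcome evaluation repeats this. Neither section says who makes the calls.

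**The concern.** The article claims a design property that its own description rules out for participants. It commits to reporting under the CONSORT extension for nonpharmacological treatments, so the claim would probably be carried into the trial report. Readers would then give the results credit for a protection that was not there.

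This matters more than usual here because the aims section names hand washing, avoiding touching the face, facemask wearing and vaccination as the primary outcomes, and all four come from the participant's own account. One of them asks how often participants noticed and stopped themselves touching their face, which leaves much to judgement. A participant who knows that they were coached may report the coached behaviour more favourably than one who was not. The only other masking described concerns what the assistants know of the purpose, and that does not address this route.

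**Working it through.** No figure of the plan is in dispute. The check is whether the blinding statement can be true under the rest of the protocol.

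**1. Active arm against control.**
- Before randomisation: participants know that there are experimental and control groups (eligibility criteria) and have the full study details (preliminary session).
- After randomisation: weekly coaching calls or none. No sham or attention-control calls are described.
- Process evaluation asks participants whether they know of friends in the other intervention or control groups. That question supposes that participants have some idea of group membership.
- Result: participants will generally know whether they are in an active arm or the control arm.

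**2. The two active arms against each other.**
- Months 0 to 3: both receive the same weekly initiation sessions. A participant could be unaware which active arm they are in.
- Months 3 to 6: calls continue in one arm and stop in the other, so the arms separate.
- Result: the 3-month comparison of the active arms could be masked to participants. The 6-month and 12-month comparisons, which bear on the hypothesis that adding maintenance helps, generally are not.

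**3. The assistants.**
- They are trained by the investigator and the project coordinator to deliver influenza-prevention sessions, so they know the topic and whom they coach.
- They could still be kept from the hypotheses and from the three-arm comparison. The statement about purpose is therefore not shown to be false.
- It is not a statement about allocation, however, and it does nothing to mask outcome assessment.

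**4. The outcome callers.**
- No section names them. Student helpers are mentioned only for the baseline questionnaire.
- The document states neither that coaches make the outcome calls nor that they do not.

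**5. What a reporting difference could do (illustration only).** The documents give no size for such a bias, so b below is assumed. From Sample size: n = 65 per group at follow-up, two-sided alpha 0.017, design effect d = 0.20. For one pairwise comparison of means with no true effect and a reporting difference of b standard deviations in favour of the active arm, the chance of a significant result in that direction is approximately

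Φ(b × √(n/2) − z), with √(65/2) = 5.70 and z = 2.387 (upper 0.0085 point).

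| b (SD, assumed) | b × 5.70 | Chance of a false significant result favouring the intervention |
|---|---|---|
| 0 | 0 | 0.017/2 = 0.85% |
| 0.1 | 0.57 | 3.5% |
| 0.2 | 1.14 | 10.6% |
| 0.3 | 1.71 | 24.9% |
| 0.5 | 2.85 | 67.9% |

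A reporting difference of 0.2 SD would equal the whole design effect. This is a simplification: the plan uses linear mixed models over four occasions, and vaccination is a yes/no outcome. The table shows how sensitive the design would be to such a bias and does not estimate the bias.

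**The case against.** Several points on the other side have force.

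- **The assistants.** A reader might infer that blinding them to the purpose is impossible and that the protocol claims they are blind to the arm. It makes no claim about the arm, and people delivering scripted sessions can be kept from the hypotheses. This stands. What remains is that such blinding is no substitute for masking outcome assessment.
- **Who collects the outcomes.** A reader might infer that coaches will ask their own participants about the behaviours they taught. The document does not say so. Staffing of calls is a detail that an article may leave to the full protocol, and the questionnaires have a setting of their own, an isolated room at the elderly centre. This stands too: the point is a safeguard worth stating and not an error found.
- **Masking is not lost everywhere.** The two active arms receive the same sessions until month 3. This is correct and limits the point.
- **Direction of bias.** A reader might infer that over-reporting occurs in the active arms only and on every outcome. The documents do not support that. Controls attend the same education session on preventive behaviours and report the same items, so they may over-report as well. Only a difference between arms would bias the comparison. It is plausible, but unproven and unmeasured. Any percentage for over-reporting would be invented.

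One could add that controls also receive outcome calls and might take these for the intervention. That is unlikely for people who have been given the full study details. None of these points makes the participant-blinding sentence true.

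**Conclusion.** The point holds in a limited form. The statement that participants are blinded to allocation conflicts with the article's own account of what participants are told and what each arm receives. It fails for active against control throughout follow-up, and for one active arm against the other after month 3. An analysis plan cannot repair this, because it concerns conduct and not analysis.

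The statement about the assistants is not shown to be wrong, but it does not protect the outcomes. With self-reported primary outcomes, differential reporting in favour of the intervention is plausible and of unknown size.

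The conclusion rests on two assumptions: that the full study details describe the arms well enough for participants to recognise theirs, and that no sham calls exist beyond what the article describes. The correction should be made. It is cheap, and it does not call for a change to the arms or to the outcomes.

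**What to change.** **Wording.** Replace the blinding sentence with a statement such as: *Participants and the assistants who deliver the telephone sessions are not blinded to allocation.* Add that participants are unaware of the study hypotheses only if the consent material supports it, since they are said to receive full study details.

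**Outcome calls.** State who makes the follow-up behaviour calls. Have them made from a fixed script by existing staff who did not coach that participant and who cannot see allocation.

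**Order of questions.** Process evaluation places questions on the acceptability of the intervention at the data collection sessions, and the answers can reveal the arm. Keep these questions until after the outcome items.

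**Record.** Note each occasion on which a caller learns a participant's arm, and report the number by arm.

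**Cost.** One changed sentence, a call rota among staff already employed, and slightly more scheduling. Staff numbers are not given in the article, so the team should confirm that the rota is workable. These steps limit the influence of the interviewer. They do not remove bias from participants knowing their own arm, which should be stated as a limitation in the report.
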